#### Statistical analyses

Data will be expressed as means ± standard deviation or numbers (percentages). Baseline characteristics will be compared using chi-squared or Fisher’s exact tests, a Student’s *t* test, or a nonparametric test as appropriate. The primary outcome, the occurrence of CPSP at 3 months, 6 months, and 1 year after surgery, will be compared using chi-squared or Fisher’s exact tests, and the relative risks and the 95% confidence interval will be calculated. All analyses of primary outcomes will be conducted using the intention-to-treat approach. A sensitivity analysis using the per-protocol approach will also be performed. In addition, a multiple logistic regression analysis will be used to identify relevant baseline covariates associated with the primary outcome. Variables tested in the model will be selected if *P* < 0.10 or if they are clinically relevant (such as usage of analgesics during surgery). All secondary outcomes are continuous variables and will be compared using the unequal-variance Student’s *t* test. Results are considered statistically significant if *P* < 0.05. Statistical analyses are performed using statistical software SPSS 17.0.

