**Methods/design:**

This is a prospective randomized controlled trial. In total, 500 adults undergoing cardiac surgery will be randomly allocated to the volatile or the TIVA group. The volatile group will receive sevoflurane or desflurane during surgery as general anesthesia. The TIVA group will receive propofol-based intravenous agents and no volatile agents during surgery. The primary outcomes will be the frequency of CPSP at 3 months, 6 months, and 1 year after surgery. In this case, CPSP is sternal or thoracic pain. It is defined as either (1) numerical rating scale (NRS) > 0 or (2) meeting all six IMMPACT criteria for CPSP. The IMMPACT criteria are validated pain instruments.

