### Outcomes

#### Primary outcome

The primary outcome is the occurrence of CPSP at 3 months, 6 months, and 1 year after surgery. CPSP is defined as sternal or thoracic pain that the patient identifies as related to their surgery in two ways: (1) NRS > 0 and (2) pain that meets all six IMMPACT criteria for CPSP. The IMMPACT criteria are validated instruments for assessing pain [28].

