### Statistics

#### Sample size estimate

The sample selected for this study was based on the finding of our prior study exploring the incidence and possible risk factors of CPSP in patients undergoing cardiac surgery with CPB via a median sternotomy. That study showed that 60.9% patients had CPSP at 3 months postoperatively [31]. The sample size for the current study is 250 patients per group, for a total of 500 patients. The study has 80–90% power to detect a 25 relative risk reduction for the primary outcome of CPSP at 3 months at a significance level (alpha) of 0.05 (two-sided), anticipating a 50–60% CPSP rate in the control (inhalation or TIVA) arm with an allowance of 10% of patients lost to follow-up, or withdrawn or withdrawing from the study.

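### Chronic pain is primary at three visits and defined in two ways, every result is judged at P < 0.05 without ranking or adjustment, so the stated 5% error rate does not hold

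*Protocol article*

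**What the plan says.** - **Visits.** The Primary outcome section states: "The primary outcome is the occurrence of CPSP at 3 months, 6 months, and 1 year after surgery". The abstract uses the plural: "The primary outcomes will be the frequency of CPSP at 3 months, 6 months, and 1 year after surgery". CPSP occurrence at 6 months or 1 year is not listed among the secondary outcomes.
- **Definitions.** The Primary outcome section defines CPSP "in two ways: (1) NRS > 0 and (2) pain that meets all six IMMPACT criteria for CPSP". The abstract words it differently: "It is defined as either (1) numerical rating scale (NRS) > 0 or (2) meeting all six IMMPACT criteria for CPSP".
- **Test and threshold.** The Statistical analyses section says: "The primary outcome, the occurrence of CPSP at 3 months, 6 months, and 1 year after surgery, will be compared using chi-squared". It names Fisher's exact test as the alternative and adds relative risks with 95% confidence intervals. Its only decision rule is: "Results are considered statistically significant if *P* < 0.05". It gives no order of testing, no adjustment and no requirement that all comparisons succeed.
- **Sizing.** The Sample size estimate section refers to a "relative risk reduction for the primary outcome of CPSP at 3 months at a significance level (alpha) of 0.05 (two-sided"), with a control rate of 50–60% and 10% loss. It does not say which definition that rate describes.

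**The concern.** The article fixes the visits, the definitions, the tests and the threshold. Taken together, they allow up to six primary comparisons, each at 0.05, while the sample size section promises an overall two-sided 0.05 for one of them. The trial wants to say which anesthetic regimen better prevents CPSP. As the plan stands, that claim could rest on one significant result among several, including one the trial was not sized for, such as IMMPACT-defined CPSP at 1 year. The plan also gives no conclusion for the case where visits or definitions disagree.

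**Working it through.** **Inputs from the article.** Three visits; two definitions; 0.05 per test; 250 per group, so 250 × 0.9 = 225 evaluable after 10% loss; control rate 50–60%; relative reduction 25 (read as 25%).

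**Assumed, because the article does not give them.** CPSP rates at 6 months and 1 year, IMMPACT-defined rates, and the correlation between visits.

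**1. The plan's own power figure (80–90%).** Two proportions, normal approximation: power = Φ[(Δ − z·SE₀)/SE₁], where SE₀ uses the pooled rate and SE₁ the separate rates. With 225 per arm and z = 1.960:
- 50% vs 37.5%: SE₀ = 0.0468, SE₁ = 0.0464; (0.125 − 0.0917)/0.0464 = 0.72, power 76.4%.
- 60% vs 45%: SE₀ = 0.0471, SE₁ = 0.0465; (0.150 − 0.0923)/0.0465 = 1.24, power 89.3%.

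With 250 evaluable per arm the results are 80.6% and 92.1%. The stated range is thus approximately met, falling short at the 50% end after losses. This shows that the calculation is for one test at 0.05. It does not affect the multiplicity point.

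**2. Number of tests.** 3 visits × 2 definitions = 6 on the wording of the Primary outcome section. On the abstract's wording as one composite, every patient meeting all six IMMPACT criteria has NRS ≥ 4 and so also NRS > 0. The composite then reduces to NRS > 0, leaving 3 tests.

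**3. Chance of at least one false positive, independent tests.**
- Six: 1 − 0.95⁶ = 26.5%.
- Three: 1 − 0.95³ = 14.3%.
- Two definitions at 3 months only: 1 − 0.95² = 9.8%.

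**4. Allowing for correlation.** The definitions are nested, but this links their tests only weakly. For rates p_N (NRS > 0) and p_I (IMMPACT), the correlation is √[p_I(1 − p_N)/(p_N(1 − p_I))]. With assumed rates of 60% and 10%, that is √(0.04/0.54) = 0.27. Patient-level simulation under no treatment effect (225 per arm, a latent pain score with nested thresholds) gave:

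| Reading | Assumptions | Risk |
|---|---|---|
| Six tests | between-visit correlation 0.3–0.95, IMMPACT rates of several percent or more | about 25% falling to 19% |
| Six tests | IMMPACT rates 1–2%, Fisher's exact test for small counts, correlation 0.5–0.95 | about 18% falling to 15% |
| Three visits, one definition | correlation 0 to 0.85 | about 14% falling to 11% (near 10% at 0.95) |
| Two definitions at 3 months | IMMPACT rates of several percent or more | about 9–10% |

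As a cruder check, six test statistics with a common correlation of 0.5 give 20.7%, and 10.8% at 0.9.

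**5. Price of a Bonferroni split over six.** Alpha = 0.05/6 = 0.0083, z = 2.638, 225 per arm:
- 50% control: (0.125 − 0.1234)/0.0464 = 0.03, power 51%.
- 60% control: (0.150 − 0.1242)/0.0465 = 0.55, power 71%.

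**The case against.** The strongest reply is that the sample size section does single out 3 months, and that success rules and multiplicity are often left to an analysis plan, which is not at hand. The first half is true, so a reader who infers that the protocol has no favored visit goes too far: 3 months is chosen for sizing, though not for inference. Even if 3 months were the only primary visit, two definitions would leave about 9–10%. The second half does not clear the plan, because the article itself keeps three visits primary and sets the threshold.

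Other stronger readings are also unsupported:
- That six tests are certain. The analysis section never says the two definitions are tested separately, and the abstract allows a three-test reading.
- That the risk is a known figure in the twenties. Only the independence figures follow from the article; the others depend on assumed rates and correlations.
- That the plan declares the trial positive if any one of six tests succeeds. It gives a per-test threshold and leaves trial success undefined.
- That NRS > 0 is documented as the powered definition. It is the likely one, since a definition requiring all six criteria would hardly reach 50–60%, but this is inference.

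**Conclusion.** The concern holds in this form: several CPSP comparisons are primary, each is judged at 0.05, and nothing ranks or adjusts them, so the stated two-sided alpha does not cover the primary claim. On six tests the risk is 26.5% under independence, about 19–25% under the assumed correlations and rates, and about 15–18% if IMMPACT cases are rare. On three tests it is about 11–14%. The exact size is uncertain because it depends on the reading and on inputs the article does not give. The direction is not: every scenario examined is clearly above 5%.

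**What to change.** 1. Reconcile the definition of CPSP in the abstract with that in the Primary outcome section, and say whether the two criteria are separate endpoints.
2. State which definition the 50–60% control rate refers to.
3. Name one primary endpoint in the abstract, the Primary outcome section and the Statistical analyses section: CPSP at 3 months, the only powered visit, under one stated definition, tested at two-sided 0.05. The sponsor should choose the definition and square it with the Study aim section, which rests on the IMMPACT criteria.
4. Test the other visits and the other definition in a prespecified fixed sequence, or report them as secondary with relative risk and 95% confidence interval and no significance claim.
5. Make the change before any unblinded comparison, date it and update the registration. The Participant timeline section reports all 500 patients enrolled by the end of June 2019, so this is a post-enrollment change and must be shown to be independent of outcome data by arm.

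**Cost.** An amendment and a registration update; no patients, and no loss of power at 3 months. The drawback of a fixed sequence is that later endpoints cannot be claimed as significant if the 3-month test fails. A Bonferroni split over six would also control the error, but at 51–71% power for the 3-month comparison, so a hierarchy is preferable.

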### Data collection

#### Baseline characteristics of patients

Demographic data, cardiac history, coexisting medical conditions, comorbidities, smoking status, EuroSCORE score, depression and anxiety history, chronic pain at presentation in an area other than the operative site, surgical procedure, intraoperative sufentanil and remifentanil dosage, and health-related quality of life measured with the 15-item Quality of Recovery Questionnaire (QoR-15) [24] will be recorded.

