#### Secondary outcomes

The secondary outcomes are: (1) NRS pain scores (0–10) 24, 48, and 72 h after surgery, (2) opioid consumption during the first 72 h after surgery, (3) the Brief Pain Inventory, the McGill Pain Questionnaire, and health-related quality of life measured with QoR-15 at 3 months, 6 months, and 1 year after surgery.

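### Follow-up QoR-15 is compared by unadjusted t test although a baseline QoR-15 is collected: a valid analysis, but less precise than the data allow

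*Protocol article*

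**What the plan says.** Under Statistical analyses, one sentence covers the whole secondary set: "All secondary outcomes are continuous variables and will be compared using the unequal-variance Student" t test. No change score, covariate or repeated-measures term is named for these outcomes. The only regression in the section serves the primary outcome: "a multiple logistic regression analysis will be used to identify relevant baseline covariates associated with the primary outcome".

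Under Baseline characteristics of patients, the recorded items include "health-related quality of life measured with the 15-item Quality of Recovery Questionnaire (QoR-15"). Under Secondary outcomes, the same instrument returns as "health-related quality of life measured with QoR-15 at 3 months, 6 months, and 1 year after surgery". The other secondary outcomes are "NRS pain scores (0–10) 24, 48, and 72 h after surgery", "opioid consumption during the first 72 h after surgery", and the Brief Pain Inventory and McGill scores at the three long-term follow-ups.

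Under Randomization, allocation, and concealment, allocation is dynamic and takes account of age, gender, EuroSCORE, predicted bypass duration and body mass index.

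**The concern.** A two-sample t test uses one value per patient and the arm label, and nothing else. For QoR-15 the trial also holds each patient's own baseline score, usually among the better available predictors of the same score later. Leaving it out puts between-patient variation that could be explained into the error term. It also leaves any chance baseline difference between the arms in the estimate.

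At stake is the width of the interval for the quality-of-life effect at each of three follow-ups. The method is stated for all secondary outcomes, so this is a choice the article makes and not a detail left open for a later analysis plan.

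**Working it through.** **Plan's own figure.** The article gives no power, SD or detectable difference for any secondary outcome, so there is nothing to reproduce. Its power statement concerns CPSP at 3 months and has no bearing here.

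**Inputs.**
- 250 patients per group with a 10% allowance for loss (Sample size estimate): 250 × 0.90 = 225 evaluable per arm.
- Test level: "at a significance level (alpha) of 0.05 (two-sided").
- Correlation r between baseline and follow-up QoR-15: not in the article. Assumed values are 0.2, 0.3, 0.5 and 0.6.
- The baseline QoR-15 is taken to be measured before allocation. This fits its heading and the statement that preoperative assessments are complete before a patient enters the trial.

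**Formulas.** With equal SDs and a common slope in the two arms, ANCOVA multiplies the variance of the arm difference by 1 − r². Hence:
- CI narrowing = 1 − √(1 − r²)
- equivalent size per arm for an unadjusted t test = 225 / (1 − r²)
- difference detectable with 80% power, in SD units = (1.960 + 0.842) × √(2/225) × √(1 − r²) = 0.264 × √(1 − r²)

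| Assumed r | 1 − r² | CI narrower by | 225 per arm acts like | Detectable difference (SD) |
|---|---|---|---|---|
| 0 (t test) | 1.00 | 0% | 225 | 0.264 |
| 0.2 | 0.96 | 2.0% | 234 | 0.259 |
| 0.3 | 0.91 | 4.6% | 247 | 0.252 |
| 0.5 | 0.75 | 13.4% | 300 | 0.229 |
| 0.6 | 0.64 | 20.0% | 352 | 0.211 |

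**The other repeated scores.** No baseline NRS, Brief Pain Inventory or McGill score is listed, so the table does not apply to them. A mixed model with arm, visit, arm × visit and unstructured covariance, without covariates and with complete data, gives per-visit arm differences equal to the simple differences in means. Any gain from repeated measures must then come from patients who have some visits but not others. As a ceiling, if the whole 10% loss were recovered at a visit, the interval would narrow by 1 − √(225/250) = 5.1%. The true gain would be smaller, because a patient lost to all follow-up contributes nothing.

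**Number of comparisons.** Counting one score per instrument, the plan has NRS 3 + opioid 1 + Brief Pain Inventory 3 + McGill 3 + QoR-15 3 = 13. A model that reports a difference at every visit yields the same 13.

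**The case against.** The strongest reply is that nothing here is wrong. Under randomisation, an unequal-variance t test at one time point is a valid comparison. It uses one value per patient, so no independence assumption is broken. With about 225 per arm, chance baseline imbalance should be small. The benefit rests on a correlation that the article does not supply, between a baseline score and scores 3 to 12 months after cardiac surgery. That correlation may be weak, and at 0.2 the interval narrows by only 2%. The outcomes are secondary.

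All of this stands, and it limits the point to efficiency. It does not remove the point: the baseline score is already collected, and adjusting for it costs next to nothing even when r is low.

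A reader might also infer more than the article supports:
- *That all repeated scores lose baseline information.* Only QoR-15 has a listed baseline.
- *That ignoring within-patient correlation is an error.* It would be if visits were pooled as independent, and the article does not say that they are. Testing each visit separately is itself only the natural reading of outcomes listed by time point.
- *That patients who miss a call are dropped.* The article does not say how missing visits are handled, and a condensed article commonly leaves this to the full plan.
- *That modelling would cut the number of tests.* It would not, as the count above shows.

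**Conclusion.** The point holds for QoR-15 only, as an avoidable loss of precision on a secondary outcome. The planned t test is valid, and the primary outcome is untouched. Baseline adjustment would narrow the QoR-15 intervals by about 2% to 20% over assumed correlations of 0.2 to 0.6. These figures assume 225 evaluable patients per arm, similar SDs and slopes in the two arms, and a baseline score taken before allocation. The percentage narrowing does not depend on the number of patients.

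For NRS, the Brief Pain Inventory and the McGill scores, a repeated-measures model is optional and helps mainly when some visits are missing. Opioid consumption over 72 h is a single total and is unaffected.

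**What to change.** In Statistical analyses, take QoR-15 out of the blanket t-test sentence and specify one of two equivalent routes:

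- ANCOVA at each of 3 months, 6 months and 1 year, with arm and baseline QoR-15; or
- one mixed model over the three visits, with arm, visit, arm × visit and baseline QoR-15.

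Include the dynamic-randomisation factors (age, gender, EuroSCORE, predicted bypass duration, body mass index) in either model. Report the adjusted difference and 95% CI at each visit, and keep the unequal-variance t test as a supportive analysis. The intraoperative opioid doses that appear in the same baseline list arise after allocation and should stay out of the model. For NRS, the Brief Pain Inventory and McGill, a mixed model without a baseline score may be added if partly missing visits are expected.

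The cost is a few lines of analysis wording and slightly more programming, with no new data, visits or patients. The Participant timeline section describes enrolment as complete and one-year follow-up as still to finish, so on that timeline the change could be dated and recorded before the final data are analysed.

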### Participant timeline

Recruitment of patients and data collection started in February 2019. Sufficient participants have been enrolled (500 patients) at the end of June 2019. The 1-year postoperative follow-up will be completed in June 2020.

### Data management and monitoring

All original data will be recorded in case report forms. The study supervisor ([name]) will supervise the conduct of the trial conduction and perform monthly audits of the trial.

## Discussion

To our knowledge, this is the first prospective randomized controlled trial to investigate the prevention of CPSP following cardiac surgery through sternotomy for patients receiving volatile anesthesia compared to those receiving propofol-based TIVA using validated pain instruments in accordance with the IMMPACT recommendations.

CPSP is defined as persistent or recurrent pain lasting longer than 3 months and without an apparent cause [32]. Our results are clinically important because the incidence of CPSP can occur in 11–56% of patients undergoing cardiac or thoracic surgery with a median sternotomy, and currently there are established methods of prevention [10–12]. As we know, general anesthesia is routinely used in cardiac surgery. To date, it is well established that propofol can improve postoperative analgesia compared with inhalational anesthesia [16, 17]. As acute pain is viewed as an initial phase of the pain response that has the potential to progress to chronic pain [5], it was assumed that propofol has the potential to prevent CPSP, though it has conflicting roles. Ogurlu et al. reported that general anesthesia with propofol was associated with reduced persistent pain at 3 months compared to sevoflurane-based anesthesia, among patients undergoing open abdominal hysterectomy [18]. Moreover, Song et al. found consistent results in patients who had undergone a thoracotomy during surgery for lung and esophageal cancer [19].

However, there is no information in the literature on the relationship between the type of anesthesia used in cardiac surgery and subsequent chronic pain. To date, no clinical trial has been published comparing the effects of volatile anesthesia with those of propofol-based TIVA on postoperative acute and chronic pain after cardiac surgery through sternotomy.

On the other hand, prior studies focusing on CPSP after either cardiac or non-cardiac surgery assessed pain using a yes or no scoring system or the NRS evaluation of the intensity of pain. Few studies have used the IMMPACT recommendations [20]. IMMPACT is a consortium of researchers and practitioners in pain medicine whose mission is to develop consensus reviews and recommendations for improving the design, execution, and interpretation of clinical trials of treatments for pain [33]. The domains of pain recommended by IMMPACT show the diversified effect of anesthetics on pain at rest, pain during activity, the quality of pain, and the physical and emotional impact of pain.

In summary, this randomized controlled trial may provide important information on the influence of these two anesthetic regimens on CPSP after cardiac surgery. Moreover, using validated pain instruments to measure CPSP in accordance with the IMMPACT recommendations will add to the currently available data on CPSP, which is important since CPSP is clinically meaningful and disturbs patients’ physical and emotional functioning and quality of life.

## Data Availability

Not applicable.

## Abbreviations

CPB: Cardiopulmonary bypass
CPSP: Chronic postsurgical pain
EuroSCORE: European System for Cardiac Operative Risk Evaluation
IMMPACT: Initiative on Methods, Measurement, and Pain Assessment in Clinical Trials
IV: Intravenous
NMDA: N- methyl-D-aspartate
NRS: Numerical rating scale
QoR-15: 15-item Quality of Recovery Questionnaire
SPIRIT: Standard Protocol Items: Recommendations for Interventional Trials
TIVA: Total intravenous anesthesia
